## Abstract

**Background:**

Non-memory-led dementias such as posterior cortical atrophy (PCA), primary progressive aphasia (PPA) and behavioural variant frontotemporal dementia (bvFTD) are low prevalent and often affect individuals under the age of 65. Tailored educational and support resources for caregivers of people living with these dementia phenotypes are scarce and unevenly distributed geographically. Web-based educational programmes are emerging as promising alternatives to improve caregiver self-efficacy and well-being. Here, we present the protocol of a study aiming to assess the feasibility of a co-produced online educational programme for caregivers of people living PCA, PPA and bvFTD: the Better Living with Non-memory-led Dementia programme.

**Methods:**

A randomised controlled feasibility trial will be conducted on a sample of 30 caregivers of people living with PCA, PPA and bvFTD. Participants will be recruited among members of the support organisation Rare Dementia Support (based at UCL in the UK). The intervention group will be given access to an 8-week co-produced web-based educational programme consisting of 6 modules addressing education about PCA, PPA and bvFTD and support strategies for the person with dementia and for the caregiver. The control group will receive treatment as usual (TAU). Feasibility will be measured through feasibility of recruitment, clinical measurement tools and acceptability. Clinical measures will be used to assess preliminary efficacy and data on completion rates, missing data and variability used to decide on measures to be included in a full-scale trial.

Allocation ratio will be 2:1 (intervention:control) stratified by diagnosis. Feasibility of recruitment and acceptability will be assessed. Clinical measures will be administered at baseline and 8-week and 3-month post-randomisation. The control group will be offered access to the intervention at the completion of data collection. Participants will be unblinded, and all measures will be self-reported online.

**Discussion:**

Online-delivered educational programmes show potential for improving care competency of caregivers and may contribute to overcoming geographical inequalities in local provision of support services. This pilot study will inform a fully powered international trial to determine the effectiveness of Better Living with Non-memory-led Dementia.

**Trial registration:**

This trial has been registered prospectively on the Clinical Trials Registry on 1st September 2022, registration number NCT05525377.

**Supplementary Information:**

The online version contains supplementary material available at 10.1186/s40814-023-01403-1.

## Background

Around 48 million people worldwide [1] live with dementia, of whom 3.9 million start with symptoms before the age of 65 (young-onset dementia) [2]. Most of the people presenting with young-onset dementia and some people with later onset dementia develop non-memory-led dementias such as the atypical forms of Alzheimer’s disease (AD) [3, 4] or frontotemporal dementia (FTD) [5]. Atypical non-memory presentations of AD involve visuospatial and language dysfunction as the main clinical manifestations at onset and, more rarely, executive or motor dysfunction [6–8]. The two most common atypical presentations of AD are posterior cortical atrophy (PCA) [9, 10], characterised by progressive deterioration of visuospatial and other posterior functions, and the logopenic variant of primary progressive aphasia (lvPPA) [11], characterised by a pattern of progressive language deterioration with impaired repetition and phonologic errors. FTD is an umbrella term that encompasses a group of clinical syndromes including the behavioural variant (bvFTD) [12] presenting with behavioural (e.g. disinhibition, apathy) and cognitive symptoms (typically executive and social cognition dysfunction), the non-fluent variant of primary progressive aphasia (nfPPA) [11] where individuals affected show non-fluent speech and agrammatism and the semantic variant of PPA (svPPA) [11] characterised by fluent speech in the context of semantic knowledge breakdown.

### Online interventions for caregivers

Low caregiving competency is associated with lower quality of life in the person with dementia [13] and with the likelihood of being admitted to a long-term care facility [14]. A decreased sense of competency is also associated with feelings of hopelessness and lower mood in caregivers [15]. Despite the proven benefits of educational programmes and skill training for caregivers, families of people with non-memory-led dementias encounter fewer opportunities to receive this type of support. This is a significant gap in care considering that many people with young-onset non-memory-led dementia are in their 50s or early 60s, which carries additional challenges about employment, financial stability and childcare responsibilities [16–18]. Finding suitable information and resources is less likely due to the lower prevalence of these phenotypes, their consequent geographical spread and their atypical symptoms [19, 20]. Caregiver’s demands for more phenotype-specific support suggest that tailored provision of education and training is a gap in the provision of care in these types of dementia.

A previous clinical trial testing, a web-based blended care self-management programme [21], showed improvements in self-efficacy, mastery and quality of life in caregivers of people with dementia. Caregivers enrolled in this intervention receive personal online coaching from a trained healthcare professional, whilst they follow four self-chosen thematic modules including psychoeducation. Coaches spend around 6 h during 8 weeks supervising caregivers using the programme. This programme has been subsequently adapted to support caregivers of people with young onset and frontotemporal dementia [22–24]. The effectiveness of these modified versions has not been tested yet in a randomised clinical trial (RCT). Moreover, web-based psychoeducational programmes that require trained healthcare professionals to be delivered (as it is the case with the aforementioned) are costly to implement and sustain.

Guided by previous research in the field, and in line with stage 1 of Medical Research Council (MRC) complex intervention development and evaluation guidance [25], a novel-manualised web-based caregiver educational programme (called Better Living with Non-memory-led Dementia) was developed alongside people living with PCA, PPA and bvFTD and their family caregivers through an iterative and collaborative process (described in the methods section). This manuscript focusses on the study protocol for an RCT to test the feasibility of this programme as recommended in stage 2 of the MRC guidelines [25, 26].

## Aims and objectives

The aim of this study is to test the feasibility of the Better Living with Non-memory-led Dementia programme. The objectives are as follows:Primary: To assess feasibility of recruitment, feasibility of measurement tools and acceptability (prospective, concurrent and retrospective).Secondary: To assess the preliminary efficacy, understood as directionality on the clinical measures (that can inform optimal outcomes measure in a full trial).

## Methods

This protocol has been registered in ClinicalTrials.org (NCT05525377) and follows the SPIRIT reporting guidelines [27] (Chan et al., 2013) adapted with supplemented and replaced sections borrowed from the CONSORT extension for pilot trials, as recommended by Lancaster and Thabane [28]. The patient and public involvement (PPI) component of this study is reported following GRIPP2-SF [29].

### Study design

This is the protocol for a pilot randomised wait-list controlled feasibility trial followed by a qualitative evaluation (mixed-method study). Participants randomly allocated to the intervention group will receive access to the educational programme for 8 weeks. Those in the wait-list control group will receive treatment as usual (i.e. pointed to Rare Dementia Support website (https://www.raredementiasupport.org/)) and access to the programme at the end of data collection. The wait-list aimed to decrease attrition and also meet ethical demands (e.g. giving caregivers access to tailored educational resources that may potentially have a beneficial effect). Outcome measures will be collected at baseline, 8-week and 3-month post-randomisation. Semi-structured interviews will be conducted after completion of the 3-month follow-up baseline measures as part of a process evaluation. The study participant flow chart is shown in Fig. 1.

**Fig. 1 Fig1:**
[figure not shown]
Participant flow chart of the Better Living with Non-memory-led Dementia feasibility trial

### Participants and research setting

People identifying themselves as caregivers of someone with PCA, PPA or bvFTD will be recruited from the Rare Dementia Support Impact project (RDS Impact) [30] and the wider Rare Dementia Support service (RDS) based in the UK. See Brotherhood et al. [30] for details on the ethical procedures and consent.

Inclusion criteria are as follows:Adults (18+) who self-identify as an unpaid caregiver (e.g. partners, children, friends) of someone with a diagnosis of PPA, PCA or bvFTD.The person with dementia is not living in a full-time care facility.The care recipient must have a confirmed diagnosis of one of these types of dementia through self-report of the caregiver (to reflect the ‘real-world’ application of the intervention).

Exclusion criteria are as follows:Poor comprehension of written English.No access to the Internet.

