### Power calculation

As this is a feasibility study, a formal power calculation is not required; however, the sample size does require justification. This study was initially intended to develop a tool for carers of people with bvFTD only. However, during the interviews with stakeholders, became apparent the need and opportunity to develop two more tools, to cover PPA and PCA (details of sample calculation for bvFTD only can be found in Brotherhood et al., [31]. Originally, we aimed to recruit 135 participants comprising 45 caregivers from each of the three diagnostic groups that the intervention is designed for (PCA, PPA, bvFTD) with a 30:15 intervention control split in a 2:1 randomisation. This would have provided both a precise estimation of the overall retention rate but also within diagnostic group. Reviewing this target once recruitment was underway, we acknowledged that this would be a large feasibility study, and with a rarer disease, it would require recruiting a large proportion of the available population. Therefore, we revised the target sample down to 30 participants (randomised 20:10 in favour of the intervention); this would allow an understanding of the trial processes, allow for adaptation and refinement of the intervention and understand acceptability and fidelity within the population. The confidence intervals on our estimates will be wider, but this is an acceptable concession given the sparsity of the potential population to recruit. We will achieve a 95% confidence interval of ±18.7% around our expected value of 76% of those completing the intervention and pre-post measures whilst viewing 70+% sessions. In terms of retention to the study, we will achieve a 95% confidence interval of ±15.5% around our expected value of 75%.

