### Randomisation

Randomisation will be provided via secure online platform hosted by NWORTH CTU, Bangor University. The randomisation procedure will be carried out by the project manager of the study ([name]). Once consent and baseline measures have been completed, the participant can be entered into the randomisation system. Randomisation will be stratified by diagnosis (bvFTD, PPA, PCA). A dynamic adaptive randomisation algorithm will be used to maintain the allocation ratio of 2:1 in favour of the intervention and the balance within stratification variables. We intend to use an unequal allocation ratio during this feasibility study due to there being more uncertainties about the interventional arm than the control arm. Development of the intervention and adjustment to the different diagnosis groups will benefit from providing more data from the feasibility study on the intervention arm specifically. The recruiting researcher will not be aware of allocations made; randomisation will be completed by a researcher independent of the other trial processes. Given the nature of this trial, participants are not blinded to group allocation. Researchers are not blinded to group allocation either, but this does not bias measure collection since measures are self-reported online. Due to the use of unequal allocation in this stage of the evaluation, it is not possible to keep analysts blind — however, given that no inferential statistics will be generated, the risk for introduction of bias at this level is minimal. The trial will be subject to internal audit and monitoring from within NWORTH CTU. Additional regular biweekly meetings of the researchers will be conducted to monitor progress and discuss any arising issues. The whole trial will be overseen by the wider research group.

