In the early stages of the development of the manuals, the work with the EbE group focused on the structure of the manuals and main messages to come across. For instance, one of our EbE with PPA wrote, ‘I would like people to understand that this is the way I speak, I have a condition, people need to be more patient’. The husband of a person with PCA said about the manuals, ‘they should be written in a positive way and convey hope’. The EbE group provided extensive advice about what symptoms to address in the programme and how, top priorities in management of symptoms, what strategies were more important to consider, they shared real situations to be include as vignettes, made suggestions about options for respite and support, identified common barriers to implement symptom management strategies and shared tips of how they had overcome them, how they managed difficult emotions (e.g. shame, guilt), deal with legal issues, relationships with others, and how they introduced companions and advice on what vocabulary to use in the manuals. The group preferred that all the material and resources from the course were also provided in a printable format (not only on the web) so people could share it with relatives and friends. The group also advised on the development of the website to host the education programme. Wireframes of the website were shared with the group either in videoconference meeting or by email, and their feedback was incorporated. In the late stages of the development process, drafts of the manuals were circulated by email for EbE to review. It was predominantly EbE who were relatives, and not people with dementia, which contributed to this last round. They sent feedback as notes in emails or direct corrections in the drafts of the manuals (either typed or handwritten). The group would also share personal resources they had found useful to understand their relative’s condition, to manage symptoms and their own well-being. Some members of the EbE group also contributed to the final proofreading.

The work of co-production took place between October 2019 and March 2022. The final draft of the manuals also received input from educational group facilitators and went through several rounds of proofreading with academic and clinical colleagues.

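### Eligibility and individual randomisation allow two carers of the same person with dementia to be allocated to opposite arms, which could contaminate a control arm of 10

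*Protocol article*

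**What the plan says.** The first inclusion criterion in Participants and research setting admits any adult who identifies as an "unpaid caregiver (e.g. partners, children, friends) of someone with a diagnosis of PPA, PCA or bvFTD". The other two concern where the person with dementia lives and the caregiver's report of a confirmed diagnosis. The exclusions are "Poor comprehension of written English.No access to the Internet". None of these refers to a second carer of the same person, and the consent and screening steps under Recruitment add no such limit. Recruitment is open to people who respond to newsletters, social media or conversations among members of one support organisation.

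The unit of allocation is the individual: "Once consent and baseline measures have been completed, the participant can be entered into the randomisation system". Diagnosis is the only stratification variable, and the algorithm is to "maintain the allocation ratio of 2:1 in favour of the intervention". Nothing links carers of the same person.

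On the material itself, the Intervention section makes every module available as a PDF. The co-production section records that the group wanted printable content "so people could share it with relatives and friends". The Procedures section gives each intervention participant a personal access link, which controls log-in but not what happens to a downloaded file.

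**The concern.** A partner, an adult child and a friend of one person with dementia each meet the criteria, and each would be randomised separately. If two of them land in different arms, the control is close to someone holding the full programme in a form that is easy to pass on. The match is also exact. Content of the manuals says the first three modules are specific to the phenotype, and two carers of one person share that phenotype. The Intervention section's own example of a practice task is explaining the disease to a friend, and friends are an eligible class of carer.

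What is at stake is the secondary objective, which reads direction of effect on the clinical measures, together with the effect sizes and standard deviations that the Statistical analysis section will use for the definitive trial's sample size. An exposed control would tend to shrink the contrast. If both carers are in the same arm there is no contamination, but their answers may be correlated.

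**Working it through.** **Inputs from the protocol.** Target 30, split 20:10; allocation 2:1; retention expected at 75% ± 15.5% and completion at 76% ± 18.7% (Power calculation). **Assumptions.** The number of same-person pairs, k, and the within-pair correlation, ρ. The protocol gives neither, so ranges are shown, starting from k = 0.

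**1. The plan's own precision figures.** Half-width = 1.96 × √(p(1 − p)/n).
- Retention: 1.96 × √(0.75 × 0.25/30) = 15.5 points.
- Completion: 1.96 × √(0.76 × 0.24/20) = 18.7 points.

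Both reproduce, with 30 and 20 independent participants respectively.

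**2. Chance that a given pair is split.** With independent 2:1 allocation: 2 × (2/3) × (1/3) = 4/9 = 44%. With a fixed 20:10 split: 2 × 20 × 10/(30 × 29) = 46%. Both are approximations to the dynamic algorithm. A pair always shares a diagnosis stratum, so balancing within strata would, if anything, make a split slightly more likely.

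**3. Chance of at least one split pair.** 1 − (5/9)^k:

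| Pairs enrolled (assumed) | At least one split | Expected split pairs (4k/9) |
|---|---|---|
| 0 | 0% | 0 |
| 1 | 44% | 0.4 |
| 2 | 69% | 0.9 |
| 3 | 83% | 1.3 |
| 5 | 95% | 2.2 |

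Under a fixed 20:10 split, the figures for one, two, three and five pairs are 46%, 71%, 85% and 96%.

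**4. Size of the contamination.** Each split pair places one exposed person among 10 controls. If that person took up the material fully and gained the full effect, the expected between-arm difference would be multiplied by 1 − 1/10 = 0.9. Two such controls give 0.8. Partial uptake gives less dilution, so these are upper limits for that number of exposed controls.

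**5. Loss of precision for retention.** Design effect = 1 + 2kρ/30; half-width = 15.5 × √(design effect).
- k = 1, ρ = 0.5: design effect 1.033, ±15.8 points.
- k = 2, ρ = 0.5: design effect 1.067, ±16.0 points.
- k = 5, ρ = 0.1: design effect 1.033, ±15.8 points.
- k = 5, ρ = 0.5: design effect 1.167, ±16.7 points.

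The worst of these adds 1.2 points to an interval that is already about 31 points wide.

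**The case against.** The strongest reply is that the harm is hypothetical. No section says that two carers of one person will enrol, or how often, and with no pairs nothing happens. The screening questions, the participant flow chart, the appendices and the parent study's protocol are not shown, and any of them might contain a one-per-family rule. This stands in part: the point must be worded conditionally. It does not remove the point, because the inclusion and exclusion lists read as complete and the rest of the article adds no limit.

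A reader might infer more than the text supports, in three ways.
- That the control arm will be contaminated. The co-production section records a preference for shareable material. It does not say that enrolled controls will receive it.
- That the stated ±15.5% is undermined. The change is at most 1.2 points with five pairs and a correlation of 0.5, and the authors openly accept wide intervals.
- That the go/no-go decision is at risk. The fixed quantitative criteria are recruitment and retention. Neither is a between-arm contrast, and both are to be read in context. Two carers withdrawing together would move retention by 2/30 = 6.7 points, but so would any two withdrawals.

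It is also fair to say that the between-arm estimates are imprecise with 10 controls whatever is done, that no inferential statistics are planned, and that a stricter rule costs recruits from a sparse population.

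**Conclusion.** The point holds as a conditional, low-severity design gap. As written, the plan permits co-carers of one person to be randomised to opposite arms and provides nothing to prevent or handle it, while the programme is issued in a form suited to sharing within a family. If one pair enrols, the chance that it is split is about 44%. Each split pair exposes one tenth of the control arm and dilutes the between-arm difference by up to about 10%.

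The consequence is confined to the secondary directionality, effect-size and standard-deviation estimates carried into the definitive trial. The primary feasibility objectives and the progression criteria are not materially affected. The conclusion rests on an unknown number of pairs, which may be zero, and on no restriction existing in the material not shown. How correlated pairs would be analysed could belong in an analysis plan and is not counted against the protocol.

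**What to change.** Add one participating caregiver per person with dementia to the inclusion criteria for further recruits, with one screening question asking whether another carer of the same person has already joined. Offer second carers access after data collection, as already planned for the wait-list. If the rule already exists in the screening items or the parent protocol, state it in the eligibility section.

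The Power calculation section says that recruitment had begun when the target was revised. Any pairs already enrolled should therefore be identified and reported with their allocations, and a sensitivity summary given that leaves out the second carer of each pair.

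The cost is one eligibility line, one question and the loss of a few second carers. With one to five pairs that is 1/30 to 5/30, or 3% to 17% of the target. Even the loss of five would leave 25/30 = 83% if all other places were filled, above the 75% recruitment threshold. If the loss is unacceptable in so sparse a population, the alternative is to allocate co-carers to the same arm and account for the pairing in the analysis. That avoids splitting pairs but gives slightly less information per participant.

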### Power calculation

As this is a feasibility study, a formal power calculation is not required; however, the sample size does require justification. This study was initially intended to develop a tool for carers of people with bvFTD only. However, during the interviews with stakeholders, became apparent the need and opportunity to develop two more tools, to cover PPA and PCA (details of sample calculation for bvFTD only can be found in Brotherhood et al., [31]. Originally, we aimed to recruit 135 participants comprising 45 caregivers from each of the three diagnostic groups that the intervention is designed for (PCA, PPA, bvFTD) with a 30:15 intervention control split in a 2:1 randomisation. This would have provided both a precise estimation of the overall retention rate but also within diagnostic group. Reviewing this target once recruitment was underway, we acknowledged that this would be a large feasibility study, and with a rarer disease, it would require recruiting a large proportion of the available population. Therefore, we revised the target sample down to 30 participants (randomised 20:10 in favour of the intervention); this would allow an understanding of the trial processes, allow for adaptation and refinement of the intervention and understand acceptability and fidelity within the population. The confidence intervals on our estimates will be wider, but this is an acceptable concession given the sparsity of the potential population to recruit. We will achieve a 95% confidence interval of ±18.7% around our expected value of 76% of those completing the intervention and pre-post measures whilst viewing 70+% sessions. In terms of retention to the study, we will achieve a 95% confidence interval of ±15.5% around our expected value of 75%.

